#### Safety outcomes

The safety outcomes included adverse event (AE) reporting, hemoglobin, liver and kidney function, electrolytes, dehydration, polyuria, nocturia, urogenital infections, (euglycemic) diabetic ketoacidosis. A general physical examination was performed at baseline and at the end of the study. Patients were specifically asked at the regular clinical visits about AEs. Each AE was registered in a standardized manner with laboratory findings in the study registry. In addition, at baseline and at week 4, calculated BUN creatinine ratio and ultrasound measurements of the inferior vena cava were employed as surrogate markers of dehydration (119, 120).

### Sample size and data analysis

#### Sample size

Based on the results of the cardiovascular heart study of Enright et al., among 2,281 community dwelling adults ≥68 years old, the expected mean 6-min walk distance (6MWD) was 344 ± 88 m which is the set target of exercise therapy in rehabilitation (45). Centered on our clinical observations and on the results of a small pilot study in the clinical rehabilitation of patients with cerebrovascular disease (121), we assumed a mean 6-MWD at baseline of 250 m with an anticipated improvement of 80 ± 40 m after 4 weeks of exercise therapy. To detect an additional difference of ±15%, as reported in previous studies on this subject (28), within the group as well as between any 2 groups with power of 80 % and an alpha error of 5% using a 2-sided test after 4 weeks, the sample size required was 130 participants per group. Based on our admission statistics, the attrition rate for administrative reasons, mainly being lack of insurance coverage for a treatment duration of at least 20 days, was estimated at 15 %, while 85 % of participants were expected to complete the week 4 follow-up. To this end, 150 participants per group needed to be enrolled (450 participants in total).

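### The 130 participants per group cannot be reproduced from the stated inputs; if the 15% is taken of the 80 m improvement, 80% power needs 176 per group and 130 gives about 67%

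*Protocol article*

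**What the plan says.** All the inputs stand in one paragraph of the protocol article, under Sample size.

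- Starting level: "we assumed a mean 6-MWD at baseline of 250 m".
- Expected change: "anticipated improvement of 80 ± 40 m after 4 weeks of exercise therapy".
- Effect sought: "To detect an additional difference of ±15%, as reported in previous studies on this subject". It is to be detected both within a group and "between any 2 groups with power of 80" percent.
- Error rate: "an alpha error of 5% using a 2-sided test after 4 weeks".
- Result: "the sample size required was 130 participants per group".
- Attrition: 15%, mainly for lack of insurance cover for a stay of at least 20 days, with 85% expected to reach week 4. The paragraph then concludes: "To this end, 150 participants per group needed to be enrolled", or 450 in total.

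The same paragraph cites 344 m (SD 88 m) from a community cohort as the target of rehabilitation. Under Data analyses, independent-samples t-tests are among the methods named for comparing changes over 4 weeks. That section also names repeated-measures ANOVAs and adjusted linear mixed-effects models, with a Bonferroni correction for the mixed models.

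**The concern.** The paragraph gives enough to attempt the calculation, and the result does not come out. The effect is given only as a percentage with no base, straight after the 80 m improvement, so a reader will take it as 15% of 80 m. On that reading 130 is about a quarter short of what 80% power requires.

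The comparison between groups is one of the study's main aims. The stated power is what a reader will use to judge a non-significant difference between two groups. If the power for the intended difference is nearer two thirds than four fifths, a null result says less than the plan implies. If the intended difference is a much larger one, the plan should say so, because the reader would then be judging against the wrong number of metres.

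**Working it through.** **Inputs (Sample size section).** Improvement 80 m; SD 40 m; effect 15%, base unstated; two-sided alpha 0.05; power 80%; 130 per group stated as required; 150 per group to be enrolled; attrition 15%.

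**Step 1. Attempt to reproduce 130 on the natural reading.** The difference is 0.15 × 80 = 12 m, so d = 12/40 = 0.30. By the normal approximation,

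n per group = 2 × (1.960 + 0.842)² × 40² / 12² = 2 × 7.849 × 1600 / 144 = 174.4, rounded up to 175.

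The exact t-test gives 175.4, rounded up to 176. The stated 130 is not reproduced.

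**Step 2. Try the other bases the section offers** (exact two-sample t-test, 80% power, two-sided 5%).

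| Reading of the 15% | Difference | n per group, SD 40 m | n per group, SD 88 m |
|---|---|---|---|
| of the 80 m improvement | 12 m | 176 | over 800 |
| of the 250 m baseline | 37.5 m | 19 | 88 |
| of 330 m at week 4 (250 + 80) | 49.5 m | 12 | 51 |
| of the 344 m reference | 51.6 m | 11 | 47 |

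Other variants with SD 40 m:

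- Within-group (one-sample) test of 12 m: 90.
- One-sided test of 12 m: 139, contrary to the stated two-sided test.
- An absolute 15 m: 113.
- 15% of the 94 m gap between 344 m and 250 m, which is 14.1 m: 128. This is the only near match, but the section never uses 94 m as the improvement; it states 80 m.

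**Step 3. Power on the natural reading** (12 m, SD 40 m, exact t-test), and the difference detectable with 80% power.

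| n per group | What it represents | Power for 12 m | Detectable difference at 80% |
|---|---|---|---|
| 127 | expected 20-day completers | 66.3% | 14.1 m |
| 130 | stated requirement | 67.4% | 14.0 m |
| 150 | everyone enrolled | 73.6% | 13.0 m |

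At 130, 14.0 m is 17.4% of 80 m (13.95/80). These figures precede any multiplicity correction. As an illustration, assuming a Bonferroni adjustment for three pairwise comparisons (alpha = 0.05/3), power for 12 m at 130 falls to about 50%.

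**Step 4. Attrition.** 150 × 0.85 = 127.5, below 130. To keep 130, enrolment must be 130/0.85 = 152.9, or 153 per group (459 in total). The figure 150 matches 130 × 1.15 = 149.5, which adds 15% where the calculation should divide by 0.85. The cost is about one point of power (67.4% to 66.3%).

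**The case against.** The strongest reply is that the base of the 15% is not stated, and that the figure is attributed to an earlier study which is not part of the documents. A reader might infer from the 67% that the design is underpowered as a matter of fact. The documents do not support that. If the 15% refers to walk distance itself (250, 330 or 344 m), 130 per group has power well above 80%. What stands in every case is that 130 does not follow from the inputs; the 67% holds only if the base is the 80 m improvement.

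A second reply is that other analyses are planned, and one of them may have produced 130. A repeated-measures between-group calculation or a baseline-adjusted analysis, each with an assumed correlation of 0.5, brings 175 down to about 131 or 132. But no correlation is stated, baseline walk distance is not among the listed adjustment covariates, and the ±40 m is already attached to the improvement. These routes show that an unreported input may lie behind 130. They do not reproduce it. An article may leave detail to a fuller protocol, but here it prints inputs and a result that do not agree.

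A third reply is correct. The 127 describes only those staying at least 20 days, which is the per-protocol set. The modified intention-to-treat set keeps anyone with one follow-up measurement whatever the length of stay, and a week-2 assessment is optional. Its size lies between about 127 and 150, so power should be given as a range.

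Finally, enrolment is closed and the article already disclaims causal conclusions. That limits the remedy to restating figures, but does not make the figures right. Nor does any passage say that null results will be read as proof of no difference; that is a risk, not a stated plan.

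**Conclusion.** The concern holds as a failure to reproduce the sample size. The figure of 130 per group does not follow from the stated inputs under any base the section offers: the candidates need 176, 19, 12 or 11 per group with SD 40 m, and 90 for the within-group test.

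On the natural reading (12 m, SD 40 m, two-sided 5%, two-sample t-test on change), the requirement is 176. Power is about 67% at 130, about 66% at 127 and about 74% at 150. This rests on the 15% being taken of the 80 m improvement, on 40 m being the SD of the change, and on no multiplicity correction. It should not be presented as the design's power unless the authors confirm that base.

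The attrition slip (150 against 153 enrolled, 127.5 against 130 completers) is real but minor.

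**What to change.** 1. In the Sample size section, state what the 15% is a percentage of, the resulting difference in metres, the SD used for it, and any correlation or adjustment behind 130.
2. If the base is the 80 m improvement, replace the claim of 80% power between groups with about 66% (per protocol, about 127 per group) to 74% (all 150) for 12 m. Equivalently, give 80% power for about 14 m (127) to 13 m (150). Say that this is before any multiplicity correction.
3. If the base is something else, show the calculation that leads from it to 130, or correct the 130.
4. Correct the attrition step: 130 completers correspond to 153 enrolled per group, and 150 enrolled to about 127.
5. State that null between-group results will be interpreted by the confidence interval against the restated detectable difference.

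The cost is wording only. Data collection ended with 450 participants, and no patients are added. On the natural reading the stated power becomes less favourable.

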#### Data analyses

Demographic data will be examined using independent-samples *t*-tests and Fisher's exact tests for dichotomous variables. Independent-samples *t*-tests and repeated-measures ANOVAs will be employed to compare changes in physical performance after 4 weeks. Differences between primary and secondary outcome variables after 4 weeks will also analyzed by linear mixed-effects models (LMMs). The time factor for the model will be set at baseline and week 4. The models will include model-based adjustments for baseline characteristics influencing physical performance in such cohorts: (1) age, sex, BMI, waist circumference, diabetes duration and history of cardiovascular disease.

To minimize the bias that could result from participants in the 3 groups having highly variable duration of stay, the prospective analyses will be performed on a modified intention-to-treat and per protocol basis. The modified intention-to-treat population will be defined as participants who have been categorized to a study group and have at least one follow-up measurement of the primary outcomes, regardless of treatment adherence or duration of stay. The “last observation carry-forward method” will be used in the absence of complete follow-up data. For “per protocol” analysis, only those participants who have follow-up measurements after a minimum treatment duration or length of stay of ≥20 days will be included.

Sensitivity analyses will be performed to account for potentially non-ignorable missing data due to dropout as well as the possible impact of other potentially influential variables. A Bonferroni correction will be applied to the LMM analyses of the primary and secondary outcomes.

Pre-specified subgroup analyses will be conducted; these will include subgroups defined according to the various entities of ASCVD, gender, age groups, and other factors.

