Given this background, the main aims of this study are firstly, to investigate the changes in physical performance and glycemic control 4 weeks after initiation of guideline-directed medical therapy of an SGLT2i and exercise therapy in patients with established ASCVD or high cardiovascular risk and T2D with initial inadequate glycemic control; secondly, to investigate the changes in physical performance and glycemic control 4 weeks after exercise therapy only in patients with established ASCVD or high cardiovascular risk and T2D with adequate glycemic control; thirdly, to investigate the changes in physical performance 4 weeks after exercise therapy only in non-diabetic patients with established ASCVD or high cardiovascular risk; and fourthly to investigate the cross-sectional and longitudinal association of glycemic control at baseline and new guideline directed antidiabetic treatment (inadequate glycemic control and diabetes + new SGLT2i vs adequate glycemic control and diabetes vs. no diabetes) with physical performance and other outcomes influencing physical performance (secondary outcomes), in patients with established ASCVD or high cardiovascular risk after adjusting for baseline covariates.

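### Baseline covariates entered as main effects in a baseline-and-week-4 mixed model do not adjust the group difference in change; covariate-by-time terms, or a model for change, are needed

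*Protocol article*

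**What the plan says.** The Data analyses section of the protocol article plans linear mixed-effects models for the primary and secondary outcomes. On the occasions in the model it says "The time factor for the model will be set at baseline and week 4", so the baseline measurement is one of the two responses. On adjustment it says "The models will include model-based adjustments for baseline characteristics influencing physical performance in such cohorts" and lists "age, sex, BMI, waist circumference, diabetes duration and history of cardiovascular disease". It lists neither a covariate-by-time term nor the baseline outcome.

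The fourth aim in the Introduction asks for the cross-sectional and longitudinal associations of the three groups with physical performance "in patients with established ASCVD or high cardiovascular risk after adjusting for baseline covariates".

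The other planned comparisons of change name no covariates: "Independent-samples *t*-tests and repeated-measures ANOVAs will be employed to compare changes in physical performance after 4 weeks".

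Two rules determine how complete the data are. The modified intention-to-treat set takes participants who "have at least one follow-up measurement of the primary outcomes, regardless of treatment adherence or duration of stay", and last observation carried forward "will be used in the absence of complete follow-up data". The per-protocol set also requires follow-up measurements.

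**The concern.** The groups are formed by glycaemic status, and group I also starts an SGLT2 inhibitor. Nothing balances age, sex, body size or cardiovascular history between them. The Discussion itself calls the selection by glycaemic control an important threat to interpretation, and it rests the study's clinical relevance partly on adjusting for variables that affect exercise capacity.

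The mixed model is the only analysis of change for which covariates are named. If the way they enter has no effect on the change contrast, the result would be labelled adjusted while any confounding of change by the listed variables stayed in it.

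A smaller, related point concerns BMI and waist circumference. Both are secondary outcomes and both are on the covariate list. In the models for these two outcomes, the same baseline number would be a response and a regressor.

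**Working it through.** The plan gives no figure of its own on this point, so there is none to reproduce. The check is algebra, then simulation.

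**1. Main effects only.** For participant i in group g, with t = 0 at baseline and t = 1 at week 4:

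Y_it = a + c_g + d·t + h_g·t + B'X_i + b_i + e_it

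where X_i are the baseline covariates and b_i is the random intercept. The within-person change is

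Y_i1 − Y_i0 = d + h_g + (e_i1 − e_i0).

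B'X_i and b_i drop out. In complete pairs the estimated difference in h between two groups is the difference in raw mean change, whichever covariates are in the model.

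**2. What is left in the estimate.** If the true change also depends on the covariates through L'X_i, the unadjusted contrast has expectation

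(h_I − h_III) + L'(mean X in I − mean X in III).

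The second part is confounding. It is removed by putting L'X_i·t in the model, or equivalently by regressing change on group and X.

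**3. Are the pairs complete?** The modified intention-to-treat set needs a follow-up value and carries the last observation forward. The per-protocol set needs follow-up. The analysed data are therefore essentially complete pairs.

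**4. Simulation.** Inputs are assumptions, not from the article: 3 × 150 participants; mean age 67, 70 and 74 years and mean BMI 31, 29 and 27 in groups I, II and III; change falling by 2 m per year of age and 2 m per BMI unit; no true group effect. By step 2 the expected unadjusted I versus III difference is −2 × (67 − 74) + −2 × (31 − 27) = 14 − 8 = 6 m. Results for one simulated data set, I versus III difference in change in metres:

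| Data | No covariates | Main effects | Covariate × time |
|---|---|---|---|
| Complete | 3.410 (SE 4.647) | 3.410 (SE 4.647) | −2.160 (SE 4.628) |
| Pairs only, 15% removed | 3.688 | 3.688 | −3.198 |
| 15% carried forward | 3.586 | 3.586 | 0.137 |
| 15% missing at random, baseline rows kept | 3.833 | 3.266 | −3.932 |

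Regressing change on group and covariates in the complete data gives −2.160, the same as the covariate-by-time model. A week-4 model with baseline walk distance and covariates gives −1.161 (SE 4.374).

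Over 40 data sets with loss depending on age and baseline distance, the mean estimates were 5.955 (no covariates), 5.975 (main effects) and 0.138 (covariate × time), against a true value of 0. With baseline-only participants kept in, main effects moved the estimate by 0.22 m on average and by at most 0.57 m. Covariate-by-time terms moved it by 5.8 m on average.

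**5. The week-4 level contrast.** In a second simulation with age as the only covariate, the group-by-time term was 8.566 with and without the age main effect. The week-4 contrast is the baseline contrast plus that term: 23.604 + 8.566 = 32.17 without age, and −13.012 + 8.566 = −4.446 with age. Main effects do change level contrasts, but all of the movement comes from the baseline part.

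**6. Range of the bias.** It is zero if there is no imbalance or if the covariates do not affect change. Under the step 4 inputs it is 14 m from age alone, −8 m from BMI alone and 6 m net. Another set of assumed inputs (130 per group, no true effect, modest imbalance) gave −11.77 m (SE 4.92) for group I versus II with and without main effects, and −0.91 m (SE 4.76) with interactions.

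**The case against.** The strongest objection is that the article nowhere says main effects only and does not name group-by-time as the target. Exact model terms are often left to a full protocol or analysis plan, and none is shown here. This stands to the extent that the point must be conditional. It does not remove the point: the article does fix the two-level time factor and the covariate list, and running that model in the ordinary way does not give what the fourth aim asks for.

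A second objection is that "Differences between primary and secondary outcome variables after 4 weeks will also analyzed by linear mixed-effects models (LMMs" can be read as a group contrast at week 4, which main effects do adjust, as they do the cross-sectional associations. That is correct, so the covariates are not idle. But baseline walk distance is not among them, so this contrast mixes differences already present at admission with differences in change.

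Third, the metre values come from chosen inputs. This stands. A reader might infer from the −11.77 m that confounding could be as large as the effect the trial was sized for. The documents do not support that: they give no imbalance and no covariate effect on change, and 12 m is the planned effect only if the ±15% is taken of the 80 m improvement, a base the sample size section does not state.

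Fourth, the Discussion rules out causal conclusions, and sensitivity analyses for other influential variables are planned. Disclosure is fair but does not turn an unadjusted estimate into an adjusted one.

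Fifth, interacting every listed covariate with time fails for diabetes duration, which is zero or undefined in group III and would be entangled with the contrasts against that group. This stands and limits the fix.

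**Conclusion.** The point holds conditionally. If the six baseline characteristics enter as main effects, the usual implementation, they leave the group-by-time estimate unchanged in complete pairs, and the covariate-adjusted longitudinal association is not obtained. They still adjust level contrasts. Equality is exact only for complete pairs, which the article's population and carry-forward rules largely ensure; with baseline-only participants retained, the shift was at most 0.57 m in the simulations.

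A reader might conclude that the plan will certainly report an unadjusted difference as adjusted. The text does not go that far, because it is silent on interactions. Nor can the size of the bias be stated: it is the covariate effect on change times the group imbalance, and both are unknown. The simulated values show the mechanism and nothing more.

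The overlap for BMI and waist circumference does not depend on the main-effects assumption. As listed, the baseline value appears on both sides of the model, so the baseline response is fully determined by a covariate and a baseline group contrast from that model has no useful meaning.

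**What to change.** - State that age, sex, BMI, waist circumference and history of cardiovascular disease each enter with a covariate-by-time term. Equivalently, regress each participant's change on group and these covariates.
- Use diabetes duration only in the group I versus II comparison. Because group II also includes participants with impaired fasting glycaemia or pre-diabetes, say how duration is coded for them.
- Add, as a sensitivity analysis, a model for week-4 walk distance with baseline walk distance and the covariates.
- For the BMI and waist outcomes, drop the matching covariate, or use a week-4 model with the baseline value as covariate only.

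The listed covariates are already collected, and the analyses are described in the future tense. The cost is a short addition to the model specification and a few more parameters.

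### Unless the baseline covariates are allowed to act on change, the two-time-point mixed model leaves the 4-week group contrast unadjusted

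*Protocol article*

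**What the plan says.** The fourth aim in the Introduction is "fourthly to investigate the cross-sectional and longitudinal association of glycemic control at baseline and new guideline directed antidiabetic treatment" with physical performance, "in patients with established ASCVD or high cardiovascular risk after adjusting for baseline covariates". The Objectives in the abstract likewise relate group to change in physical performance.

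The Data analyses section gives the model meant to deliver this: "Differences between primary and secondary outcome variables after 4 weeks will also analyzed by linear mixed-effects models (LMMs"). It continues: "The time factor for the model will be set at baseline and week 4". On adjustment it says "The models will include model-based adjustments for baseline characteristics influencing physical performance in such cohorts" and lists "age, sex, BMI, waist circumference, diabetes duration and history of cardiovascular disease".

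The section does not say whether these enter as main effects or also in interaction with time. It writes out no group-by-time term, and it does not say whether the model's target is a difference in change or in week-4 level. The other analyses of change carry no stated covariates: "Independent-samples *t*-tests and repeated-measures ANOVAs will be employed to compare changes in physical performance after 4 weeks".

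**The concern.** Baseline is one of the two outcome times in this model, and every listed covariate is a baseline characteristic, so it is constant within a person. A main effect for such a covariate moves a participant's baseline and week-4 values by the same amount and cannot influence the modelled change. The group-by-time term answers the longitudinal part of the fourth aim, and it would be the same with and without the covariates.

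The groups are formed by glycaemic status and not by randomisation, and the Discussion itself treats this selection as an important threat to interpretation. A result labelled as adjusted would then carry whatever confounding of change by age, sex, body size or cardiovascular history the crude comparison has.

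**Working it through.** **Inputs from the protocol article.** Two outcome times and six covariates fixed at baseline (Data analyses). The modified intention-to-treat set requires at least one follow-up value, with the last observation carried forward, so participants with a baseline value have both time points. Expected gain 80 m with SD 40 m, an additional difference of 15%, and 130 per group before attrition (Sample size).

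**Step 1, algebra.** With main-effect covariates X, group g, random intercept b and time t = 0 or 1:

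Y(t) = a_g + βt + γ_g·t + δ'X + b + e(t)

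Y(1) − Y(0) = β + γ_g + e(1) − e(0)

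Both X and b cancel. With both values present, the estimate of γ_I − γ_II is the raw difference in mean change. If a term κ'X·t is added, the change becomes β + γ_g + κ'X + e(1) − e(0). This is the regression of change on group and covariates.

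**Step 2, numerical check.** Random-intercept fits to simulated data, 3 × 150 participants. The following are assumptions, not figures from the documents: no true group effect on change, Group I on average 5 years younger than Group II, gain falling 1 m per year of age. Built-in confounding is therefore 5 × 1 = 5 m. All six covariates were included, with diabetes duration set to 0 in Group III. Mean Group I versus II contrast in change over 20 data sets:

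| Model | Contrast (m) |
|---|---|
| No covariates | 5.89 |
| Main-effect covariates | 5.89 (largest gap from unadjusted 5 × 10⁻¹²) |
| Covariate-by-time terms | 1.06 |
| Change regressed on group and covariates | 1.06 |

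The standard error of a single adjusted estimate was about 4.29 m, so the mean of 20 has a Monte Carlo error of about 4.29/√20 = 0.96 m. The 1.06 m is compatible with the true value of 0. The shift of 5.89 − 1.06 = 4.83 m is close to the 5 m built in.

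**Step 3, when the cancellation is exact.** In one data set with carried-forward values the contrast was 3.498 m both without covariates and with main effects, and −2.598 m with covariate-by-time terms. With 15% of week-4 values missing and not imputed, the cancellation was only near: 4.393 versus 4.310 m in one data set, with a largest gap of 0.45 m over 20.

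**Step 4, what main effects do adjust.** In one complete data set the Group I versus II level contrast moved from 0.40 to −3.32 m at baseline and from 3.12 to −0.60 m at week 4. The change contrast stayed at 2.71 m. The adjusted week-4 level contrast is the adjusted baseline contrast plus the crude change: −3.317 + 2.713 ≈ −0.60 m.

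**Step 5, size.** Confounding left in = covariate gap × effect of the covariate on gain. The documents give neither factor. If age has no effect on gain it is 0 m. With an assumed 1 m per year and an assumed gap of 3 to 5 years it is 3 to 5 m. As a scale, 15% of 80 m is 12 m, so this is 3/12 = 25% to 5/12 = 42%. The standard error of a difference in mean change is 40 × √(2/130) = 4.96 m, so the bias is about 0.6 to 1.0 standard errors. The 12 m is one reading of the 15%. It does not reproduce the plan's 130 per group, since 12 m with SD 40 m needs 175 at 80% power and two-sided 5%. It serves here only as a yardstick.

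**The case against.** The strongest reply is that the two conditions for cancellation, main effects only and a group-by-time target, are nowhere written. A condensed article may leave the form of the covariate terms to an analysis plan that is not shown. That stands as far as it goes. A reader might infer that the plan prescribes an unadjusted longitudinal result, or that the listed covariates do nothing. The text supports neither: the wording is compatible with covariate-by-time terms, and the adjustment does act on the cross-sectional association and on a week-4 level contrast.

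It is also fair that the covariate list is not the only control of confounding. Percent of predicted 6-MWD is a primary outcome, chosen because groups may differ in age, sex and BMI. Subgroup analyses by ASCVD entity, gender and age are planned, as are sensitivity analyses for other influential variables. These help only in part. Percent predicted divides distance by a predicted value and does not equalise gains between groups. Subgroups take one factor at a time, and the sensitivity analyses are not described.

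Finally, the 3 to 5 m rests on assumed inputs, and the simulation was built to contain confounding. It shows which models remove it, not that it is present. False-positive rates computed at an uncorrected 5% level would not be the plan's own, because a Bonferroni correction is to be applied to these models.

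**Conclusion.** The point holds in conditional form. If the six covariates enter as main effects, the longitudinal association with change promised "after adjusting for baseline covariates" equals the raw difference in mean change. This is exact when both time points are present, as carrying the last observation forward ensures for anyone with a baseline value, and close to exact otherwise. Only level contrasts are adjusted. Main effects are the plainest reading of the text, and under it the plan does not deliver its own fourth aim.

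The practical size is unknown: 0 m if the covariates do not affect gain, about 3 to 5 m under the stated age assumptions. The documents do not show that the eventual estimate will be biased, or by how much.

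**What to change.** Name the group-by-time contrast, the difference between groups in 4-week change, as the longitudinal target. Add covariate-by-time terms for age, sex, BMI, waist circumference and cardiovascular history. Equivalently, when both values are present, regress 4-week change on group and these five covariates. Report this estimate beside the unadjusted one.

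Keep diabetes duration out of the three-group model and use it only in the Group I versus II contrast. In Group III it is zero or undefined by the group's definition, so its time interaction would overlap with the group effect. Group II also admits participants with pre-diabetes, so the coding of duration for them should be stated.

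The cost is about five degrees of freedom, one per interaction if each covariate enters as a single term, and no new data. In the complete simulated data set the standard error of the Group I versus II contrast rose from 4.17 to 4.29 m, about 3%, with all six interactions included.
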